#### MRI data preprocessing

2.6.2

MRI preprocessing will be conducted using DPABISurf 1.8 (based on fMRIPrep), SPM12, GRETNA for network analysis, and the FMRIB Software Library (FSL) for diffusion tensor imaging analysis.The rs-fMRI preprocessing steps include: (1) slice timing correction; (2) motion correction; (3) co-registration to structural T1 images; (4) nuisance regression (motion parameters, white matter, and CSF signals); (5) spatial normalization to MNI space; (6) band-pass filtering (0.01–0.08 Hz); and (7) spatial smoothing with a 6 mm FWHM Gaussian kernel.

Participants with excessive head motion (> 2.5 mm translation or > 2.5° rotation) will be excluded from further analysis. In addition, framewise displacement (FD) will be calculated as a quality-control metric to assess motion during scanning, and scans with excessive motion (e.g., mean FD > 0.5 mm) will be carefully inspected.

#### rs-fMRI metrics

2.6.3

ALFF and ReHo.Group comparisons will be performed using voxel-wise two-sample t-tests with Gaussian Random Field (GRF) correction (voxel-level p < 0.001, cluster-level p < 0.05).Functional Connectivity (FC).Seed regions include the bilateral anterior insula, dorsal anterior cingulate cortex (dACC), amygdala, thalamus, and nodes of the salience network.

Analytic steps include: (1) extraction of seed time series; (2) computation of Pearson correlation matrices; (3) Fisher’s Z-transformation; and (4) group comparison of FC maps using GRF correction.

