#### Behavioral and questionnaire data

2.6.1

All behavioral, clinical, and questionnaire analyses will be performed using SPSS 26.0 and R 4.3.0.Group comparisons: Continuous variables (HCT accuracy, time estimation performance, MAIA, BPQ, TMT, AFT, DSST) will be compared using independent-samples t-tests or Mann–Whitney U tests for non-normal distributions. Categorical variables will be analyzed using χ² tests.All analyses will control for age, sex, years of education, and medication dosage (chlorpromazine equivalents). In analyses involving HCT accuracy, time estimation performance will additionally be included as a covariate to control for potential confounding effects related to temporal estimation ability. Additional sensitivity analyses will examine whether group differences in HCT accuracy remain significant after controlling for time estimation performance.Correlation analyses: Within each group, associations between interoceptive accuracy, subjective measures (MAIA/BPQ), PANSS scores, and cognitive performance will be examined using Pearson or Spearman correlations with FDR correction.

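### No covariate list for the resting-state group maps includes head motion: framewise displacement is computed for quality control only, so a residual motion difference between groups would go unadjusted

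*Protocol article*

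**What the plan says.** Section 2.6.3 (rs-fMRI metrics) fixes the test for ALFF and ReHo: "Group comparisons will be performed using voxel-wise two-sample t-tests with Gaussian Random Field (GRF) correction", with a voxel-level threshold of 0.001 and a cluster-level threshold of 0.05. For FC, the last analytic step is "group comparison of FC maps using GRF correction"; no test, model or covariate is named.

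Motion is handled in section 2.6.2 (MRI data preprocessing), in three ways:
- Within each participant's time series: "nuisance regression (motion parameters, white matter, and CSF signals".
- By exclusion: "Participants with excessive head motion (> 2.5 mm translation or > 2.5° rotation) will be excluded from further analysis". Section 2.4.6 adds that datasets failing quality control are excluded under predefined criteria.
- By FD, whose role is stated as follows: "framewise displacement (FD) will be calculated as a quality-control metric to assess motion during scanning". The only consequence given for a high value is this: "scans with excessive motion (e.g., mean FD > 0.5 mm) will be carefully inspected".

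The only explicit covariate list is in section 2.6.1, under behavioral and questionnaire data: "All analyses will control for age, sex, years of education, and medication dosage (chlorpromazine equivalents". Analyses of HCT accuracy also adjust for time estimation. Section 2.6.5 mentions covariates for the brain–behavior models without naming any. Motion appears in neither place.

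**The concern.** A two-sample t-test attributes the whole mean difference at a voxel to diagnosis. If patients and controls who pass quality control still differ in how much they moved, and the metric varies with motion, part of that difference is motion.

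The planned safeguards do not remove this. Regressing motion parameters works within a participant and need not remove everything that varies between participants. The exclusion limits remove the worst scans but leave a range of motion below them. Gaussian random field correction controls clusters that arise by chance; a systematic shift is not chance.

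The article therefore computes the measure needed for adjustment and then leaves it out of the inference. At stake is the exploratory aim of characterizing abnormal intrinsic activity and connectivity in schizophrenia, and of relating it to behavior, symptoms and cognition. The limitations in the Discussion mention medication and the lack of cardiac and respiratory recording, but not residual head motion.

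**Working it through.** The plan gives no figure to reproduce on this point. The check has a textual part and an illustration.

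**Textual check: where could motion enter a group-level comparison?**

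| Place | What it covers | Motion as a covariate? |
|---|---|---|
| 2.6.1 | Behavioral, clinical and questionnaire analyses; age, sex, education, chlorpromazine equivalents | No, even if read as reaching imaging |
| 2.6.2 | Time-series regression, exclusion limits, FD for inspection | Not at group level |
| 2.6.3 | ALFF and ReHo: two-sample t-test; FC: model not named | No |
| 2.6.5 | Brain–behavior models; covariates not named | Not stated, and not the group maps |

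**Illustration: how large could the effect be?**

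Inputs:
- n = 30 per group (section 2.3).
- Voxel-level threshold 0.001 (section 2.6.3), taken as two-sided.
- Assumed, not in the documents: group difference in mean FD, δ = 0.3 to 0.8 within-group SD.
- Assumed, not in the documents: within-group correlation of FD with the metric, r = 0.2 to 0.4.
- No true disease effect.

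Step 1. The spurious standardized difference is d = r × δ. Lowest: 0.2 × 0.3 = 0.06. Highest: 0.4 × 0.8 = 0.32.

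Step 2. The t statistic has 30 + 30 − 2 = 58 degrees of freedom and noncentrality d × √(30/2) = d × 3.873. For d = 0.06 this is 0.232; for d = 0.32 it is 1.239.

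Step 3. The false-positive rate at one voxel is the probability that |t| exceeds the two-sided critical value under that noncentral t distribution.

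| δ | r | d | Rate at 0.001 | Multiple of 0.001 |
|---|---|---|---|---|
| 0 | any | 0 | 0.0010 | 1 |
| 0.3 | 0.2 | 0.06 | 0.0013 | 1.3 |
| 0.5 | 0.3 | 0.15 | 0.0032 | 3.2 |
| 0.8 | 0.3 | 0.24 | 0.0081 | 8.1 |
| 0.8 | 0.4 | 0.32 | 0.0175 | 17.5 |

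For a single test at 0.05, the same four non-zero values of d give 0.056, 0.088, 0.150 and 0.230. That is not the planned threshold, so these rates do not describe the planned maps.

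Step 4. The same settings were simulated (100,000 runs each) with mean FD added as a covariate. The rate returned to about 0.001 at the 0.001 level and about 0.05 at the 0.05 level. This assumes that FD acts linearly with the same slope in both groups.

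Step 5. Cost in precision. In those simulations, the variance of the adjusted group difference relative to the unadjusted one was 0.88 (δ = 0.3, r = 0.4), 1.00 (0.3, 0.2), 1.00 (0.8, 0.4) and 1.14 (0.8, 0.2). The worst case widens the standard error by √1.14 − 1, about 7%.

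The rates are per voxel. A cluster-level rate was not computed; it would need the spatial pattern of the motion effect.

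**The case against.** **The wording may be shorthand.** Section 2.6.1 also names t-tests and then says that all analyses are adjusted, and the Discussion speaks of statistical control of medication effects in connection with neural as well as behavioral outcomes. So age, sex and education may already be intended for the maps. This stands, and it would be too strong to say that the maps are meant to be wholly unadjusted. It does not close the gap, because motion is on no list.

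**The t-test is stated for ALFF and ReHo only.** A reader might infer that FC and TBSS are also fixed as two-sample t-tests. Sections 2.6.3 and 2.6.4 name no test for them, so there the model is unspecified.

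**Quality control may be stricter than it looks.** A reader might infer that a scan with mean FD above 0.5 mm stays in the analysis. The text says only that it is inspected, and section 2.4.6 excludes datasets that fail predefined criteria, so its fate is not stated.

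**Nothing says that patients move more.** It is tempting to say that motion is confounded with diagnosis in every map. That needs a group difference in FD, which the documents neither report nor predict.

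**The carry-over is not established.** A reader might infer that significant clusters feed the brain–behavior models. Section 2.6.5 lists neural indices without saying how they are selected.

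**Supplementary material is not shown.** Supplementary Figures 1 and 2 or a fuller plan might list group-level covariates. If so, a line in section 2.6.3 would settle the point. But the article does not simply leave this open: it names the ALFF and ReHo test and gives FD a role in quality control only.

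**Adjustment is not free of bias.** If motion tracks illness severity, conditioning on FD can remove true signal. This stands and is addressed in the fix.

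**Conclusion.** The point holds for the resting-state group maps. Followed as written, the plan compares ALFF and ReHo with an unadjusted test and FC with an unnamed model, and motion is a group-level covariate in neither. Preprocessing and exclusion reduce the problem without ensuring that residual motion is balanced.

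The size cannot be known from the documents. Under the assumed ranges, the per-voxel false-positive rate at the 0.001 threshold is about 1.3 to 17.5 times nominal; with no FD difference it is nominal. The result supports adjusting in advance. It does not show that the maps will be wrong.

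The change is worth making before the maps are seen, but its reach is limited: the imaging outcomes are declared exploratory and are to be interpreted cautiously, and the primary HCT outcome is unaffected.

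**What to change.** In section 2.6.3, replace the two-sample t-test, and complete the FC step, with one statement: group differences in ALFF, ReHo and FC maps are tested in a voxel-wise general linear model with group, mean FD, age, sex and years of education, at the existing Gaussian random field thresholds. Report mean FD by group. Show the unadjusted maps as a sensitivity analysis, so that readers can see what adjustment removes if motion and illness are related. Also state what follows when an inspected scan has high FD.

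For TBSS (section 2.6.4) the same approach is optional. The test there is not specified and no diffusion motion summary is planned, so it would need an extra processing step as well as a change of wording.

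Cost: a few sentences and four degrees of freedom (four covariates). FD is already computed for the resting-state scans. For the FD term, precision ranges from a small gain to a standard error about 7% wider under the assumptions above.

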#### DTI analysis

2.6.4

DTI data will be processed using FSL. The following diffusion indices will be extracted: fractional anisotropy (FA), mean diffusivity (MD), radial diffusivity (RD), and axial diffusivity (AD).

Tract-Based Spatial Statistics (TBSS) will be used to create a white-matter skeleton, followed by group comparisons with FDR correction.

Although the present analyses focus on conventional DTI metrics (FA, MD, RD, and AD), the multi-shell acquisition protocol also provides the possibility of applying advanced diffusion models, such as Neurite Orientation Dispersion and Density Imaging (NODDI) or constrained spherical deconvolution (CSD), in future analyses to further characterize white matter microstructure. Advanced diffusion modeling approaches, such as NODDI, have increasingly been applied to characterize microstructural abnormalities in schizophrenia (28, 29).

#### Multimodal brain–behavior integration

2.6.5

Integrated analyses will evaluate relationships among neural indices (ALFF, ReHo, FC, FA, MD, RD, AD), interoceptive accuracy (HCT), subjective interoceptive awareness (MAIA, BPQ), clinical symptoms (PANSS, HAM-A, HAM-D), and cognitive performance.

Statistical methods will include multiple linear regression and partial correlations (controlling for covariates), with Bonferroni or FDR correction applied for multiple comparisons. The MRI preprocessing pipeline is illustrated in **Supplementary Figure 1**.

#### Handling of missing data

2.6.6

Missing data will be addressed using pairwise deletion for correlation analyses and multiple imputation when missingness exceeds 5%.

A study-specific Case Report Form (CRF) was developed to ensure standardized acquisition of demographic, clinical, interoceptive, cognitive, and MRI-related data. The complete CRF is included as a **Supplementary File**. The full multimodal analysis pipeline is provided in **Supplementary Figure 2**.

## Discussion

3

This protocol outlines a comprehensive and multimodal investigation into interoceptive dysfunction in schizophrenia, integrating behavioral performance, subjective awareness, clinical characteristics, cognitive assessments, and multimodal neuroimaging. Building on our previous meta-analysis demonstrating significant impairments in interoceptive accuracy and sensitivity in individuals with schizophrenia, this study is positioned to extend prior work by examining the neurobiological substrates underlying these deficits. The proposed design allows systematic characterization of intrinsic neural activity, functional connectivity, and white-matter microstructure within interoception-related circuits, including the anterior insula, dorsal anterior cingulate cortex, amygdala, and thalamo-cortical pathways.

By incorporating both objective behavioral measures (heartbeat counting task) and subjective assessments (MAIA and BPQ), the study adopts a multidimensional approach aligned with contemporary theoretical models of interoceptive processing. The integration of clinical and cognitive assessments further enables examination of how interoceptive dysfunction relates to symptom domains and functional outcomes. Understanding these relationships may provide insight into the mechanistic links between altered bodily self-awareness, emotional dysregulation, and disturbances in self-processing—features central to the psychopathology of schizophrenia. The neuroimaging component is designed to provide critical insights into the neural mechanisms underpinning interoceptive impairment. Resting-state fMRI metrics such as ALFF, ReHo, and seed-based connectivity will offer complementary perspectives on intrinsic neural activity and large-scale network organization, while diffusion tensor imaging will allow evaluation of white-matter microstructure supporting interoceptive signaling. These multimodal neuroimaging measures may help identify neural signatures associated with interoceptive deficits, contributing to the development of imaging-based biomarkers for schizophrenia.

Importantly, this study may also have clinical implications. By identifying specific brain regions and networks associated with interoceptive dysfunction, this study may help clarify the neural mechanisms underlying altered bodily self-processing in schizophrenia. Such mechanistic insights could inform the development and refinement of targeted interventions, including body-awareness-based and mindfulness-based approaches, which are thought to engage interoceptive and self-regulatory neural systems. In addition, identifying neural correlates of interoceptive deficits may help guide neuromodulation strategies by providing potential circuit-level targets for intervention and enabling more mechanistically informed and personalized treatment approaches.

Several considerations should be acknowledged. As a cross-sectional protocol, the study will not permit causal inferences regarding the directionality between interoceptive dysfunction and neural abnormalities. Although medication effects will be statistically controlled, they may still influence behavioral and neural outcomes. Antipsychotic medications may affect autonomic nervous system function, including heart rate and heart rate variability, which could potentially influence performance on interoceptive tasks such as the heartbeat counting task. Although medication dosage will be statistically controlled using chlorpromazine equivalents, residual medication-related effects cannot be completely excluded and should be considered when interpreting the findings.

Additionally, the relatively modest sample size may limit statistical power for detecting subtle neural effects or conducting reliable individual-level or subgroup analyses. Although the planned sample size is consistent with comparable multimodal neuroimaging studies, neuroimaging findings in this study should therefore be interpreted with caution. Accordingly, the primary analyses will focus on group-level comparisons and brain–behavior associations, which provide greater statistical robustness and are commonly used in neuroimaging research with similar sample sizes. Neuroimaging analyses in this protocol are primarily exploratory and will be interpreted cautiously with appropriate correction for multiple comparisons.

Furthermore, T1-weighted structural MRI will be used to assess brain morphology, diffusion tensor imaging will be used to evaluate white-matter microstructure, and resting-state functional MRI will be used to measure blood-oxygenation-level-dependent (BOLD) signal fluctuations, which represent indirect physiological indicators of neural activity rather than direct neuronal activity. In addition, concurrent cardiac and respiratory signals were not recorded during MRI scanning, which prevented the implementation of physiological noise correction methods such as RETROICOR. Finally, the neuroimaging protocol includes only resting-state fMRI rather than task-based paradigms specifically targeting interoceptive processing. Task-based paradigms may provide more direct evidence of neural responses to interoceptive signals; however, resting-state fMRI was selected to reduce task-related burden and potential performance variability in individuals with schizophrenia, who may experience difficulties maintaining attention or completing complex tasks during MRI scanning. Future studies may incorporate task-based interoceptive paradigms to further investigate neural responses to interoceptive signals.

## Glossary

ACC: Anterior cingulate cortex
AD: Axial diffusivity
AFT: Animal Fluency Test
ALFF: Amplitude of low-frequency fluctuations
BPQ: Body Perception Questionnaire
CPZ-equivalent: Chlorpromazine-equivalent antipsychotic dose
CSF: Cerebrospinal fluid
DTI: Diffusion tensor imaging
DSST: Digit Symbol Substitution Test
FA: Fractional anisotropy
FC: Functional connectivity
FDR: False discovery rate
FSL: FMRIB Software Library
FWHM: Full width at half maximum
GRETNA: Graph Theoretical Network Analysis Toolkit
GRF: Gaussian random field correction
HAM-A: Hamilton Anxiety Rating Scale
HAM-D: Hamilton Depression Rating Scale
HCT: Heartbeat Counting Task
MAIA: Multidimensional Assessment of Interoceptive Awareness
MD: Mean diffusivity
MNI: Montreal Neurological Institute standard space
MRI: Magnetic resonance imaging
PANSS: Positive and Negative Syndrome Scale
r-sfMRI/rs-fMRI: Resting-state functional magnetic resonance imaging
RD: Radial diffusivity
ReHo: Regional homogeneity
SPM: Statistical Parametric Mapping
TMT: Trail Making Test
WM: White matter.
